##### Pregnancy experience

Pregnancy experience will be measured by the Dutch translation of the Pregnancy Experience Scale (PES; [68]), ‘Beleving van de Zwangerschapsschaal- verkorte versie’ [55]. Of the total scale, consisting of the two subscales Uplifts (positive pregnancy experiences) and Hassles (negative pregnancy experiences), only the 10-item Uplift scale will be used in this study. Examples of items are ‘How much the baby is moving’ and ‘Making or thinking about nursery arrangements’ and participants will be asked the extent to which a particular experience makes them happy, answered on a 4-item Likert scale ranging from 0 (not at all) to 4 (very much). Higher scores indicate a more positive pregnancy experience. The BZS-K Uplift scale has good internal consistency (*α* = .83) and good intraclass correlation coefficients (*ICC* = .72–.84; [55]).

##### Intrinsic motivation

Intrinsic motivation for behavior change will be asked by five questions based on questions from the Treatment Self-Regulation Questionnaire (TSRQ) [69]. Examples of questions are ‘I think that quitting smoking is best for my health’ and ‘I think that quitting smoking is best for the health of my baby’ answered on a five-point Likert scale ranging from (1 = totally disagree, 5 = totally agree). Higher scores indicate higher intrinsic motivation to quit smoking. Internal consistency of the TSRQ was found to be acceptable [69].

#### Covariates

##### Level of addiction

The ‘Heaviness of Smoking Index’ (HSI; [70]) will be used to assess the level of smoking addiction of the women. The question on the number of cigarettes smoked on a day in combination with a question asking about the time to first smoking in the morning generates the ‘Heaviness of smoking index’. The question on time to first smoking can be answered with ‘within 5 minutes’ (3 points), ‘after 6-30 minutes’ (2 points), ‘31 to 60 min’ (1 point), or ‘after 60 minutes’ (0 points). To create a total HSI score, the answer to the question about the number of cigarettes smoked on a day are categorized in four groups and each group will be given a different amount of points: 0 (10 or fewer), 1 (11 to 20), 2 (21–30), 3 (31 or more). Scores of the two questions will be summed in order to obtain three levels of addiction; low addiction (score between 0 and 2), moderate addiction (3, 4), high addiction (5, 6).

##### COVID 19-related stress

COVID-19-related concerns will be assessed using self-constructed questions. Participants will be asked to answer questions such as “Have you been infected by the COVID-19 virus?” (yes/no), “How much do you worry about the COVID-19 virus?”, and “How much do you worry about your own health and the health of your unborn child?”, which can be answered on a scale from 0 (Not worried at all) to 10 (Extremely worried). From the scale questions a sum score will be calculated with higher scores indicating more COVID-19-related concerns.

##### History of psychological complaints

History of psychological complaints will be asked using three self-constructed questions, i.e. “Did you receive treatment for psychological complaints in the past year?” (yes/no), and if so, “For which complaints have you been treated?” and “Do you still experience complaints?” (yes/no). Answers to these questions will be categorized in 0 (never received treatment), 1 (history of treatment), 2 (currently experiencing complaints).

##### Depression symptoms

Depression symptoms will be assessed using the 7-item ‘Depression’ subscale of the Depression, Anxiety, Stress Scale-21 (DASS short form; [71, 72]). Participants are asked to indicate the extent to which they had experienced specific symptoms over the previous week on a 4-point Likert scale ranging from 0 (Never) to 3 (Most of the time). Higher scores indicate higher levels of depressive symptoms. Internal consistency of the depression subscale has found to be good (Cronbach’s ﻿α = .91; [71]).

##### Reasons of smoking

Reasons of smoking will be asked with six self-constructed questions, e.g. ‘I smoke because it makes me calm’ and ‘I smoke because I am bored’ (1 = totally disagree, 5 = totally agree).

##### Birth characteristics

Complications and hospitalization during and after childbirth of the mother and child will be asked by questions such as “Did you have any complications during delivery?” and “Was your baby admitted to the hospital immediately after birth or in the first week after birth?”. When answered “yes”, questions will appear asking about the type of complications and reason for hospitalization.

In order to improve comprehension of specific parts of the questionnaires were adapted to our target group, consisting of women of lower SES. Some items under ‘Experienced stress’, ‘Depression’, ‘Intrinsic motivation’ are adapted. Also, answer categories of ‘Experienced stress’, ‘Self-efficacy regarding smoking cessation’ (0 = never to 3 = always) and ‘Perceived mother-child bond’ were reduced or adapted to increase consistency among questionnaires and to improve clarification.

### Statistical analyses

The study will be performed according to the Consolidated Standards of Reporting Trials (CONSORT) Statement (see Fig. 3). All analysis will be done in SPSS version 26.0 and ﻿RStudio version 1.1.456 and a significance level of 0.05 will be used. Analyses will be performed conforming to intention-to-treat analysis, so that all randomized participants will be analyzed. We will explore baseline data to examine differences between the two different conditions and between the study completers and drop-outs. We will control for relevant covariates (i.e. SES, treatment history, maternal age, gestational age at birth, level of addiction, birth complications, way of delivery) by adding them to the models. Prior to the main analyses, outliers will be checked. Demographic outcomes will be compared using chi-square tests and independent sample t-tests.

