### Sample size calculation

To ensure acceptable power for the main analysis of the intervention effect on smoking cessation at post-intervention, an a priori sample size calculation was performed by the program G*Power [54]. Using a power of 80% an alpha of 0.05 and an F-test, we need to include 160 participants (80 participants in each arm) in order to be able to detect a small difference (effect size of 0.20) between the intervention group and the control group on the primary outcome measure, smoking cessation at t1.

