### Procedure

The participants will be informed about the study via obstetric practices, gynecologists, or general practitioners, but can also sign up for participation by own registration via a form on the project’s website. Pregnant women, who are visiting their health professional, will be given a brief explanation via a flyer. Women, who are willing to participate, will be asked to scan the QR-code on the flyer and will then be directed to an online registration form where they will fill in the contact details. This information will then be sent to a secured mailbox which can only be accessed by the main researcher. Subsequently, registered participants will be called by the researcher or research assistant who will explain the study in more detail. If participants are willing to participate they will be sent an information letter and consent form, which they will be asked to read, sign and send back. Then, women will be called to screen for exclusion criteria. Eligible women will receive an invitation email with a link to the first online questionnaire (t0). Participants will be assigned an identification number, which will be used throughout the study. To ensure confidentiality, the file including both the participants’ names and identification numbers will be saved with a password that can only be accessed by the principal researcher. After completion of the t0 questionnaire, participants will be randomized. This will be done by sending an email to an independent researcher who has access to the randomization list. The randomization list is created with blocks of 2, 4, and 6 participants, each containing equal numbers of participants allocated to the intervention and active control group, using an online randomization program. The independent researcher will send an email with information about the assigned group. Participants assigned to the intervention group receive an email with a link to download the application on their smartphones. The control group will be sent a link to the website with the psycho-education module, which they can access as frequently as they desire. After 8 weeks, participants will receive an invitation to complete the second questionnaire (t1). Two follow-up questionnaires will be sent, the first at two weeks after birth (t2) and the other at three months after birth (t3). Participants will receive 7.50 euros on their bank account for each completed questionnaire.

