### Outcome measures

At four different time points, women will receive online questionnaires. Each questionnaire will take approximately 15–20 min to complete. The first questionnaire is a baseline questionnaire (t0, before randomization) including the main outcomes and demographic information (i.e. date of birth, weeks of pregnancy, ethnicity, educational level, employment status, relationship status, smoking behavior partner, living conditions). Eight weeks and one day after group assignment, participants will receive the second questionnaire (t1), through which post-intervention measurements will take place. Follow-up questionnaires will be sent two weeks after birth (t2) and three months after birth (t3). In Fig. 1, an overview of the outcome measurements for each time point is depicted. Prior to t1, t2, and t3, a screening question will appear asking about the health of the baby. In case of pregnancy loss or if the baby died after birth, participants will be advised to quit the study participation. They will still receive the agreed compensation for the completed questionnaires.

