**Fig. 3 Fig3:**
[figure not shown]
Consolidated Standards of Reporting Trials (CONSORT) flow diagram

To examine the effectiveness of the eHealth intervention on the primary outcome, the number of women who quit smoking during pregnancy measured at post-intervention and follow-up, General Estimating Equations (GEE) using a logistic model will be performed. Potential covariates that will be included in the model are maternal age, depressive symptoms, gestational age, employment status, education level, level of addiction, and partner’s smoking status. To investigate the effectiveness of the intervention on secondary outcomes (i.e., smoking behavior, perceived stress, birth outcomes, negative affectivity, self-efficacy, mother-child bonding, intrinsic motivation, parenting self-efficacy, pregnancy-related anxiety) linear mixed models will be performed for each outcome variable separately. Furthermore, we will test whether the effect of the intervention (independent variable) on smoking cessation (dependent variable) is mediated by a change in perceived stress using a GEE model. Moreover, it will be tested whether program usage and experience, self-efficacy regarding smoking cessation, feelings of mother-child bonding, intrinsic motivation for life style behavior change, and pregnancy experience moderate the effect on smoking cessation (primary outcome), smoking behaviour, and perceived stress by adding the variables to the GEE model.

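### The plan does not secure use of the t0 value of the outcome in the mixed models for secondary outcomes, so the treatment contrasts may be less precise than the data allow

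*Protocol article*

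**What the plan says.** The Statistical analyses section of the protocol article gives a covariate list for the models in general: "We will control for relevant covariates (i.e. SES, treatment history, maternal age, gestational age at birth, level of addiction", then birth complications and way of delivery. The outcome's own t0 value is not among them.

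Below Fig. 3 in the same section, a second list of potential covariates follows the sentence on the primary GEE, before the secondary outcomes are introduced. It belongs to the primary model. For the secondary outcomes the text says only that "linear mixed models will be performed for each outcome variable separately". It does not say which waves form the response, or how the arms' t0 means are treated.

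The t0 data exist. Under Outcome measures: "The first questionnaire is a baseline questionnaire (t0, before randomization) including the main outcomes and demographic information". Under Procedure, women are randomised only after completing the t0 questionnaire. The uses of baseline data that the analysis section does state are to compare the arms and to compare completers with drop-outs.

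**The concern.** For a continuous scale, the outcome's own pre-randomisation value is usually its strongest single predictor. The general list is introduced as a definite enumeration, and this predictor is not in it. If the mixed models do not bring t0 in some other way, intervals will be wider than they need be in a trial of 80 per arm.

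Perceived stress is where this matters most, since it is both a secondary outcome and the proposed mediator. Pregnancy-related anxiety, parenting self-efficacy and cigarettes per day are the other candidates. The text is also compatible with several models of quite different precision, so the estimator is not settled in advance.

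**Working it through.** **The plan's own figure.** The only sample-size figure is for the primary outcome: "Using a power of 80% an alpha of 0.05 and an F-test", "we need to include 160 participants (80 participants in each arm") to "detect a small difference (effect size of 0.20"). The metric is not named. Read as Cohen's f in a two-group F-test, 0.20 needs about 200 women, and 160 gives 71% power. So 160 does not reproduce from the stated inputs alone. Nothing below depends on that; I take only the 80 per arm from it.

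**Inputs**
- n = 80 per arm (Sample size calculation). Equal allocation (Procedure: "each containing equal numbers of participants allocated to the intervention and active control group").
- Two-sided alpha 0.05 (Statistical analyses: "a significance level of 0.05 will be used").
- r, the correlation between t0 and follow-up: not in the document. Assumed 0.3, 0.5 and 0.7, the same between all waves.
- For power only, a true difference of 0.4 SD. This is an assumption. It equals f = 0.20 for two equal groups, but the document does not state it for any secondary outcome.
- Complete data and equal SD at each wave (assumed).

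**Formulas.** The variance of the between-arm contrast at t1, in SD units, is (2/80) × k. The factor k depends on how t0 is used:
- t1 to t3 only, no t0: k = 1
- t0 in the response, separate t0 means by arm, difference in change: k = 2(1 − r)
- t0 as a covariate, or t0 in the response with one common mean: k = 1 − r²

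The second minus the third is 2(1 − r) − (1 − r²) = (1 − r)², which is positive for every r below 1. A generalised least squares calculation over four waves gave the same factors, and the two versions of the third option agreed exactly.

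Detectable difference at 80% power = (1.96 + 0.84) × √(2k/80) = 0.443 × √k. Power for 0.4 SD is from the noncentral t with 158 df and noncentrality 0.4 × √(40/k).

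| Use of t0 | r | k | Detectable difference (SD) | Power for 0.4 SD |
|---|---|---|---|---|
| t1 to t3 only | any | 1.00 | 0.44 | 71% |
| Change contrast | 0.3 | 1.40 | 0.52 | 57% |
| Change contrast | 0.5 | 1.00 | 0.44 | 71% |
| Change contrast | 0.7 | 0.60 | 0.34 | 90% |
| Covariate or common t0 mean | 0.3 | 0.91 | 0.42 | 75% |
| Covariate or common t0 mean | 0.5 | 0.75 | 0.38 | 83% |
| Covariate or common t0 mean | 0.7 | 0.51 | 0.32 | 94% |

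Simulation of 3,000 trials per setting agreed to within about one percentage point.

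Put as sample size, at r = 0.5 an adjusted analysis of 0.75 × 160 = 120 women is as precise as either of the other two analyses of 160.

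**The case against.** The strongest objection is that no loss is shown. A mixed model over repeated waves often carries t0 in the response, where a covariate list would not reveal it. With a common t0 mean it recovers the whole gain. Some wording points towards t0 being used: Trial design counts it among four waves, smoking behaviour is to be compared between time points, and the mediator is a change in perceived stress. The article is also condensed, and model detail is often left to a fuller plan.

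Much of this stands. A reader might infer that the trial discards its baseline scores, but the document does not say so. It is silent on the response vector. A reader might also count both covariate lists against the secondary models, but the second belongs to the primary GEE.

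The objection does not dispose of the point. The sentence that assigns linear mixed models also covers birth outcomes and negative affectivity, which have no t0 value, so naming the model class does not place t0 in the response. The wording about change suggests a change contrast as readily as a common-mean model, and the change contrast is less precise than adjustment at every r below 1. Only one of the ordinary specifications avoids a loss, other than adding the covariate, and the article does not state it.

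**Conclusion.** The point holds as a conditional statement about precision. The general list omits the t0 outcome value, and the description of the secondary models does not say how t0 is used. Unless t0 is in the response with a common mean, the contrast is less precise than baseline adjustment would make it. Relative to adjustment, the variance is higher by a factor of 1.10, 1.33 or 1.96 (1.00 divided by 0.91, 0.75 or 0.51) if t0 is left out. It is higher by 1.54, 1.33 or 1.18 (1.40/0.91, 1.00/0.75, 0.60/0.51) for a change contrast, at r = 0.3, 0.5 and 0.7. If the full plan already uses a common t0 mean, nothing is lost.

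Limits:
- The correlations, the 0.4 SD effect and complete data are assumptions.
- A reader might infer bias or a threat to the main result. Neither follows: every contrast compared here is unbiased under randomisation, and every woman smokes at entry, so t0 smoking status cannot sharpen the primary analysis.
- Birth outcomes and infant temperament have no t0 value and are outside the point.
- For cigarettes per day the gain is smaller, because level of addiction is in the list and already contains that number in categories.
- The measurement schedule (Fig. 1) is not visible here, so collection at t0 cannot be checked scale by scale.

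**What to change.** Add one sentence to the analysis of secondary outcomes. For each continuous outcome measured at t0 (such as perceived stress, pregnancy-related anxiety, parenting self-efficacy and cigarettes per day, as the schedule allows), do one of the following:
- enter its t0 value as a covariate, with t1 to t3 as the outcomes; or
- keep t0 in the response and constrain the two arms to one common t0 mean.

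Report the between-arm difference at each follow-up from that model. Leave birth outcomes and infant temperament out of this rule.

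The cost is the sentence. No new data are needed, and t0 should be essentially complete because randomisation follows it. The choice should be recorded before outcome data are compared by arm. If a fuller plan already contains the common-mean model, stating so closes the point.

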## Introduction

Worldwide, substantial numbers of women who smoke, continue to smoke during pregnancy. Recently estimated prevalence of smoking pregnant women in the European Region was 8.1%, which was the highest percentage when compared to the world average of 1.7% [1]. Even though prevalence rates of pregnant smoking women have been decreasing over the years [2], these numbers are yet of concern for several reasons. Maternal smoking has serious implications for the developing fetus and the mother. Maternal smoking increases the risk of miscarriage [3], premature delivery, lower birth weight [4], and congenital abnormalities [5]. Among the single newborns born in the Netherlands with small-for-gestational age, 17% of the cases was found to be related to maternal smoking during pregnancy [6]. Negative effects of prenatal maternal smoking are not only observed in the early years of the child, but have also been associated with negative health outcomes later in life, such as asthma [7] and obesity [8]. Moreover, maternal smoking during pregnancy has been linked to reduced academic achievement and decreased cognitive abilities of children [9, 10] and to neurobehavioral problems in childhood [11–13].

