### Participants and recruitment procedure

Participants will be recruited through midwifery practices, specialized departments of hospitals in the Netherlands and through advertisements on reliable websites focusing on pregnancy over a 1.5-year period (July 2020–February 2022). Health care professionals will be offered flyers to hand out to potential participants. Additionally, they will receive an information sheet with the inclusion criteria, short sentences for study explanation, and a list of frequently asked questions so that they can easily explain the study to potential participants. Women are eligible for participation if they are older than 18 years, are less then 28 weeks pregnant (to enable intervention completion in view of the risk for premature birth in pregnant smokers), if they smoke on a regular basis (at least smoking 1 day/week), have an intention to quit smoking during pregnancy, and if they have sufficient command of the Dutch language. Women with severe psychiatric disorders, women who abuse other drugs (e.g. alcohol, cannabis, cocaine, and GHB), and who are participating in other intensive stop-smoking interventions will be excluded from participation. The focus of our recruitment will be on women with low SES. However, women with high SES are also allowed to participate.

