##### Birth outcomes

Birth outcomes such as gender, birth date, gestational age and weight at birth will be assessed with self-constructed questions. Moreover, 1- and 5-min Apgar scores will be asked. These scores can be found in a booklet that women usually receive after delivery in the Netherlands. In case these scores are unknown to the women, consent will be asked to contact the midwifery practice in order to obtain these scores.

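### Three birth variables, one of them a study outcome, are listed as covariates without limiting which models they enter; in the birth-outcome models, adjusting for them does not estimate the intervention's total effect

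*Protocol article*

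**What the plan says.** All the relevant text is in the protocol article.

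- **General adjustment rule** (Statistical analyses, first paragraph): the trial will control for "SES, treatment history, maternal age, gestational age at birth, level of addiction, birth complications, way of delivery) by adding them to the models". No model is excepted. The same paragraph commits to intention to treat, with every randomised woman analysed.
- **Primary model** (Statistical analyses, paragraph after Fig. 3): the logistic GEE has a separate list: "Potential covariates that will be included in the model are maternal age, depressive symptoms, gestational age, employment status, education level, level of addiction", followed by the partner's smoking status. Gestational age carries no time point here. The paragraph then names birth outcomes among the secondary outcomes to be tested for an intervention effect in linear mixed models.
- **Timing** (Procedure; Participants and recruitment procedure): "After completion of the t0 questionnaire, participants will be randomized", and eligible women "are less then 28 weeks pregnant".
- **Outcome status** (Birth outcomes, under Secondary outcomes): "Birth outcomes such as gender, birth date, gestational age and weight at birth will be assessed with self-constructed questions".
- **Birth complications** (Birth characteristics, under Covariates): "Complications and hospitalization during and after childbirth of the mother and child will be asked by questions".
- **Causal premise** (Introduction): "Maternal smoking increases the risk of miscarriage [3], premature delivery, lower birth weight [4]."

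**The concern.** A randomised comparison is protected by adjusting only for what was fixed before allocation. Three of the seven variables in the general list are known only once the baby is born. If the intervention works as intended, it changes smoking, and on the article's own account smoking changes the timing of birth. Gestational age at birth then carries part of the benefit. Holding it constant in a model for birth weight asks what the intervention does apart from any effect on prematurity. That is a different and smaller quantity than the effect the secondary objective is about.

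The second issue is that the section contains two adjustment lists that are not reconciled. Their wording (*relevant*, *potential*) leaves room to settle the adjusted primary result after the data are seen.

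**Working it through.** The plan states no figure on this point, so there is none to reproduce. The check is one of timing and role, followed by illustrations on assumed inputs.

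**1. Timing and role of the three variables**

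| Variable | Known when | Also an outcome? | Link to smoking stated in the article? |
|---|---|---|---|
| Gestational age at birth | at birth, after randomisation | yes | yes (premature delivery) |
| Birth complications | at or after birth | no, listed as a covariate | not stated |
| Way of delivery | at birth | no | not stated |

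So 3 of 7 covariates post-date randomisation, and 1 of those 3 is an outcome.

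**2. The two lists side by side**

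- General list only: SES, treatment history, gestational age at birth, birth complications, way of delivery.
- GEE list only: depressive symptoms, undated gestational age, employment status, education level, partner's smoking. Education and employment overlap in substance with SES.
- Clearly in both: maternal age and level of addiction.

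**3. Birth weight (assumed inputs)**

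Suppose quitting (Q) changes gestational age by *g* SD, and birth weight = 0.6 × gestational age + 0.2 × Q + noise, in SD units. The share of the quitting effect that runs through gestational age is 0.6*g* / (0.6*g* + 0.2):

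- *g* = 0.2: 0.12/0.32 = 37.5%
- *g* = 0.4: 0.24/0.44 = 54.5%
- *g* = 0.8: 0.48/0.68 = 70.6%

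Simulation with 400,000 women per scenario, adjusting for gestational age at birth and complications, gave these arm differences:

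| *g* | Unmeasured shared cause | Unadjusted (SD) | Adjusted (SD) | Removed |
|---|---|---|---|---|
| 0.2 | yes | 0.048 | 0.030 | 38% |
| 0.4 | yes | 0.064 | 0.027 | 58% |
| 0.8 | yes | 0.097 | 0.025 | 74% |
| 0.4 | no | 0.069 | 0.032 | 54% |
| 0.8 | no | 0.104 | 0.026 | 75% |

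A second simulation in grams assumed that quitting adds 0.3 to 1.0 week and that each week adds 150 g. Adjusting for gestational age at birth alone took 22.9 to 15.8 g (31% removed), 26.2 to 15.3 g (42%) and 38.1 to 14.4 g (62%). Together the two give roughly 30% to 75%.

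**4. Smoking status (assumed inputs)**

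Odds ratio for abstinence, without and then with gestational age at birth and complications in the model:

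| True effect on quitting (log odds) | Direct effect of arm on gestational age | t1 OR | t3 OR |
|---|---|---|---|
| 0.8 | none | 2.05 → 2.10 | 1.26 → 1.24 |
| 0.8 | 0.2 SD | 2.07 → 1.91 | 1.26 → 1.15 |
| 0.8 | 0.4 SD | 2.03 → 1.55 | 1.24 → 0.99 |
| 0.8 | 0.4 SD, stronger shared cause | 1.90 → 1.40 | 1.21 → 0.91 |
| 0 | 0.2 SD | 1.01 → 0.91 | 1.00 → 0.92 |
| 0 | 0.4 SD | 1.00 → 0.80 | 1.00 → 0.85 |

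When the arm acts on gestational age only through quitting, the t1 estimate barely moves. The separate simulation in grams agrees: its log odds ratio went from 0.84 to 0.85–0.86. Material change needs a second route.

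**5. Women kept under case deletion**

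With 160 women who all have t1 data, and an assumed fraction *m* lacking birth data, a GEE containing a birth covariate keeps 160 × (1 − *m*) women: 144 for *m* = 10%, 128 for 20% and 112 for 30%. Without the birth covariate it keeps all 160. The article gives no value for *m*. It does say, under Outcome measures, that women with pregnancy loss or infant death are advised to leave the study, so some such women are to be expected.

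**The case against.** The strongest reply is that the primary analysis is untouched. Its model has its own list, which omits complications and way of delivery. A model-specific list would ordinarily take precedence over a general sentence. Weeks of pregnancy is collected at t0, so reading the undated gestational age as a baseline value is natural. This largely stands: the article does not establish that birth variables enter the primary GEE. It shows only that the two paragraphs have to be reconciled.

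A reader might infer that the t1 smoking result, on which the trial is sized, is biased. The documents do not support that. Birth normally follows t1, so these variables are consequences of smoking status at t1 and do not mediate it. The material shifts in the illustration require a direct route from arm to gestational age. The app does train stress reduction, so such a route is conceivable, but the article states none.

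A reader might also infer a definite loss of women from the primary analysis. That depends on case deletion and on attrition rates the article does not give. Imputation would avoid the loss, and missing-data handling may sit in an analysis plan not shown. Nor does any passage say the two lists will be combined, so a charge of overfitting from their sum has no footing.

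Finally, no analyst would regress gestational age on itself, and *relevant* could be read as leaving discretion. That softens the literal reading for that one model. It does not help the birth-weight model, where adjustment for gestational age at birth could easily be made in good faith under the rule as written.

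**Conclusion.** The concern holds for the birth-outcome models and may extend to other t2 and t3 outcomes. The written rule conditions a treatment comparison on post-randomisation variables, one of which is an outcome. Followed for birth weight, it would remove roughly 30% to 75% of the intervention's total effect. That range rests entirely on assumed effects of quitting on gestational age and birth weight. There would be no such distortion if the intervention changed neither the birth variables nor their causes. For complications and way of delivery, the objection rests on timing alone, since the article states no causal link from smoking.

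For the primary GEE the finding is an ambiguity between two lists. If birth variables did enter and cases were deleted, women with t1 data would be lost, against the commitment to analyse everyone randomised. Bias in the t1 effect would probably be small unless a second route to gestational age exists.

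**What to change.** - Remove gestational age at birth, birth complications and way of delivery from the adjustment set of every treatment-effect model. Keep them as outcomes or descriptive variables. A birth-weight analysis adjusted for gestational age at birth may be reported if it is labelled exploratory.
- Restrict adjustment to variables measured at t0.
- State that gestational age in the primary GEE means gestational age at t0.
- Replace the two lists with one fixed in advance, and drop *relevant* and *potential*. Which t0 variables it holds is the sponsor's choice.

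The cost is about two sentences of analysis text. Weeks of pregnancy is already collected at t0, so no new data or patient burden is involved.
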